## Abstract

**Background:**

Most low-risk pregnant women receive the standard model of prenatal care with frequent office visits. Research suggests that a reduced schedule of visits among low-risk women could be implemented without increasing adverse maternal or fetal outcomes, but patient satisfaction with these models varies. We aim to determine the effectiveness and feasibility of a new prenatal care model (OB Nest) that enhances a reduced visit model by adding virtual connections that improve continuity of care and patient-directed access to care.

**Methods and design:**

This mixed-methods study uses a hybrid effectiveness-implementation design in a single center randomized controlled trial (RCT). Embedding process evaluation in an experimental design like an RCT allows researchers to answer both “Did it work?” and “How or why did it work (or not work)?” when studying complex interventions, as well as providing knowledge for translation into practice after the study. The RE-AIM framework was used to ensure attention to evaluating program components in terms of sustainable adoption and implementation.

Low-risk patients recruited from the Obstetrics Division at Mayo Clinic (Rochester, MN) will be randomized to OB Nest or usual care. OB Nest patients will be assigned to a dedicated nursing team, scheduled for 8 pre-planned office visits with a physician or midwife and 6 telephone or online nurse visits (compared to 12 pre-planned physician or midwife office visits in the usual care group), and provided fetal heart rate and blood pressure home monitoring equipment and information on joining an online care community.

Quantitative methods will include patient surveys and medical record abstraction. The primary quantitative outcome is patient-reported satisfaction. Other outcomes include fidelity to items on the American Congress of Obstetricians and Gynecologists standards of care list, health care utilization (e.g. numbers of antenatal office visits), and maternal and fetal outcomes (e.g. gestational age at delivery), as well as validated patient-reported measures of pregnancy-related stress and perceived quality of care. Quantitative analysis will be performed according to the intention to treat principle. Qualitative methods will include interviews and focus groups with providers, staff, and patients, and will explore satisfaction, intervention adoption, and implementation feasibility. We will use methods of qualitative thematic analysis at three stages. Mixed methods analysis will involve the use of qualitative data to lend insight to quantitative findings.

**Discussion:**

This study will make important contributions to the literature on reduced visit models by evaluating a novel prenatal care model with components to increase patient connectedness (even with fewer pre-scheduled office visits), as demonstrated on a range of patient-important outcomes. The use of a hybrid effectiveness-implementation approach, as well as attention to patient and provider perspectives on program components and implementation, may uncover important information that can inform long-term feasibility and potentially speed future translation.

**Trial registration:**

Trial registration identifier: NCT02082275

Submitted: March 6, 2014

**Electronic supplementary material:**

The online version of this article (doi:10.1186/s12884-015-0762-2) contains supplementary material, which is available to authorized users.

## Background

Prenatal care is a key preventive health service used in developed countries around the world. By providing expectant mothers with regular health evaluations and information about the course of the pregnancy, labor, birth, and parenthood, prenatal care aims to reduce the risk of unfavorable pregnancy and birth outcomes. Most prenatal care occurs in the setting of routine office visits. In the U.S., the American College of Obstetricians and Gynecologists (ACOG) recommends a uniform prenatal visit schedule comprised of approximately 14 visits: every four weeks up to 28–32 weeks of gestation, then every two weeks up to 36 weeks, and finally weekly until birth [1]. This rhythm of care has been codified largely based on tradition that is informed by a plan of care directed at the detection of risks such as hypertensive disorders of pregnancy. However, research does not necessarily support high numbers of visits for the majority of low-risk pregnancies [2, 3]. Indeed, there is a wide variation in visit schedules across countries, and higher numbers of visits do not necessarily correspond with better outcomes [3]. While there is no doubt that prenatal care is important to maternal and fetal health, there is limited evidence of an exposure-response relationship between visit frequency and outcomes [4].

In 1989, the Expert Panel on the Content of Prenatal Care issued recommendations for prenatal care that were based on expert review and consensus of the limited best available evidence [5]. These included a recommendation that the visit schedule be flexible and based on the needs of each expectant mother, for example more visits for nulliparous and high-risk women and fewer visits for multiparous and low-risk women. Subsequently, several studies have considered the effectiveness of reduced antenatal care schedules. Most have found that a reduced schedule of visits among low-risk women could be implemented without increasing adverse maternal or fetal outcomes such as preterm delivery, preeclampsia, and low birth weight [6–12], although there is mixed evidence on perinatal mortality [11, 13]. Some studies found patient satisfaction was unchanged [6] or improved [9, 10], but a larger number suggest that patient satisfaction decreases with lower numbers of visits [7, 8, 11, 14].

Reasons for reduced satisfaction are unclear. Sikorski et al. found patients receiving a reduced schedule were less likely to feel listened to and more likely to want more time to talk at visits [7]. More than 50 % of the study participants felt that some gaps between visits were too long. Novick’s qualitative assessment of women’s preferences for prenatal care included continuity of care, flexibility, comprehensiveness of care (including access to group discussions with other pregnant women), developing meaningful relationships with professionals, and becoming more active participants in care [15]. Structural barriers like inconveniences of office visits can limit women’s access to prenatal care [16].

Since the expert panel’s report 25 years ago, and despite general consensus on the safety and effectiveness of a reduced visit schedule on maternal and fetal outcomes, new models that address women’s preferences have not been widely adopted [17]. Some investigators suggest that the effectiveness of prenatal care should not be defined solely in terms of risk assessments and number of prenatal office visits, but rather in terms of the content of the care [18, 19]. New models of care that address access and continuity of care while reducing the burden of pre-planned office visits could result in increased patient satisfaction. However, there is limited research on new models that go beyond adaptation of the visit schedule.

### Developing a new model of care

In 2011, members of the Obstetrics Division at Mayo Clinic (Rochester, MN), together with the Mayo Clinic Center for Innovation (CFI) design team, developed a new model of care for low-risk pregnancies that reduced office visits while increasing virtual connections with nurses and providers. This prenatal care program (OB Nest) was to be based on proactive and direct support from a nursing team that could meet the on-demand needs of expectant mothers as they arise, redesigning the need for and timing of planned on-site appointments with providers while increasing expectant mothers’ experience of and satisfaction with their care.

Their theory of action was that the traditional model of prenatal care predates methodological and technological advances in pregnancy monitoring and communications, assuming a rhythm of care dependent on face-to-face visits that preceded an appreciation for the busy lives of women. Furthermore, it engendered the idea that the prenatal office visit is the sole intended point of contact for expectant mothers with their care team, shifting the locus of control to the provider as in disease treatment models, thus medicalizing the pregnancy experience. Pregnant women may associate the high frequency of visits in the traditional model with safe pregnancy outcomes. In developing the OB Nest care model, the team hypothesized that empowering low-risk pregnant women to retain more control of their prenatal care shifts their health care delivery from a sickness model to a wellness model.

As a result, the team designed and rapid-tested potential components of the new program (summary information available at www.mayo.edu/center-for-innovation/projects/ob-nest/). The following were selected for inclusion in OB Nest: Online Care Communities, At-Home Measurement, Video Appointments (with the option of phone where video is not available), and Proactive Calls. This paper reports the study protocol for the evaluation of the OB Nest program (Fig. 1).

**Fig. 1 Fig1:**
[figure not shown]
OB Nest intervention components

### Study purpose

The purpose of this study is to determine the effectiveness of the OB Nest program, compared to usual prenatal care in this practice, and to evaluate the implementation process. The primary research and evaluation questions are as follows:Does OB Nest improve patient-reported satisfaction with care, as well as pregnancy-related stress and perceived quality of prenatal care?Does OB Nest reduce the rate of in-clinic health care utilization without impacting maternal/fetal outcomes or fidelity to the process of care standards specified by ACOG?Can OB Nest be implemented as intended during the study, and can it be feasibly adopted into practice?

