### Sample size

On average 2400 pregnant women receive prenatal care from the Obstetrics Division in a 12-month period, and about 60 % of these are considered to be low-risk pregnancies. We will enroll 300 patients in this study (150 patients per arm). This accounts for a withdraw/post-randomization exclusion rate as high as 10 %, so the effective sample size can be as low as 135 patients/arm. Sample size calculations are displayed in Table 2.

**Table 2 Tab2:** Sample size calculations

Outcome	Estimated rate for standard of care^a^	Improvement to be tested/expected	Power
Patient-reported outcomes			
Satisfaction with care	108.4 (SD 14.4)	115.6	98 %
Perceptions of quality of care	83.9 (SD 22.8)	91.9	86 %
Prenatal stress	12.9 (SD 7.1)	16.5	98 %
Maternal/fetal outcomes and standards of care			
Low birth weight	11 %	6 %	24 %
Gestational age at delivery	38.9 (SD 2.5)	40.2	99 %
Standard of prenatal care (measured as receiving at least 20 out of 24 items from the ACOG standards of prenatal care list)	90 %	95 %	30 %
Health care utilization			
Number of antenatal visits	14.7 (SD 4.2)	12	99 %

Abbr: ACOG = American Congress of Obstetricians and Gynecologists

^a^All calculations 2-sided with alpha of 0.05. Continuous outcomes compared to a half of standard deviation increase

We will interview up to 40 patients and conduct approximately 4 patient focus groups of 10–12 participants each. We will also interview physicians (*n* = 6) and conduct focus groups with midwives (*n* = 9), nurses (*n* = 7), and desk staff/clinical assistants (*n* = 10) at three points in time. This sample size is within standards for qualitative research, but we will increase the sample size if needed to achieve saturation in identifying themes.

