### Analysis plan

#### Quantitative (QUAN)

Quantitative analysis will be performed according to the intention to treat principle, including all participants in the arm to which they were randomized, regardless of whether they received the intervention assigned or crossed over to the other treatment arm. Baseline characteristics will be reported in the study results with continuous values being reported as means and standard deviations and categorical values reported as counts and frequencies and compared between study arms using t-tests and chi-squared tests, respectively.

We will use standard techniques appropriate for participant level randomized trials, with each outcome compared between study arms using t-tests for continuous outcomes and chi-square tests for dichotomous outcomes. Any baseline imbalances (*p* < 0.05) will be explored as a possible factor to adjust for when the outcome measures are analyzed. We will use predetermined criteria for missing data when calculating scores on patient-reported surveys. The comparison of outcomes will be considered significantly different between arms at a *P* < 0.05.

Participants who move into a high risk category after 12 weeks will stay on study and be evaluated in the arm to which they were randomized. If more than 10 % of patients choose to crossover from intervention to control, a sensitivity analysis will be conducted. Trial enrollment, completeness of data collection, and fidelity of follow-up procedures will be reviewed and reported during study team meetings which will be conducted on a monthly basis. Analysis of quantitative data will be performed at the close of the study.

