### Expected impact

We are currently enrolling patients in this study. Upon completion of this study we will have gained an understanding of whether this new model of prenatal care improves patient-reported outcomes, supporting the clinical team’s theory of action related to what women want in prenatal care. It will also provide evidence on whether this model is safe and effective in changing the paradigm of health care utilization toward interventions delivered by expert registered nurses and away from provider-focused care. This is a critical factor as health care institutions endeavor to improve care while controlling costs.

This study has the potential to increase uptake of new models of reduced visit care, which has faltered even since the Expert Panel on the Content of Prenatal Care recommendation in 1989. Hybrid designs and evaluation frameworks like RE-AIM focus studies like this on external validity and the translatability of evidence-based practice by including methods to understand implementation [20, 25, 38]. We also aim to add to the growing literature on embedding process evaluations and qualitative methods in RCTs [39, 40] by addressing the value of these methods starting in pre-trial planning and fully reporting how each method is to be used and why each was selected.

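### Research question 2 asks for no worsening of maternal/fetal outcomes and ACOG fidelity, but the only stated rule is a two-sided difference test at P < 0.05, which cannot support that answer

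*Protocol article*

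**What the plan says.** Study purpose lists, among the primary research and evaluation questions, whether OB Nest reduces in-clinic utilization "without impacting maternal/fetal outcomes or fidelity to the process of care standards specified by ACOG".

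The quantitative analysis plan has "each outcome compared between study arms using t-tests for continuous outcomes and chi-square tests for dichotomous outcomes", with P < 0.05 as the threshold for calling the arms different. The article gives no margin and no confidence-interval criterion for these outcomes.

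Table 2 (Sample size) heads its effect column "Improvement to be tested/expected", and its footnote states "All calculations 2-sided with alpha of 0.05". The relevant rows are:

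| Outcome | Usual care | Target | Stated power |
|---|---|---|---|
| Low birth weight | 11% | 6% | 24% |
| ACOG standard of care | 90% | 95% | 30% |
| Gestational age at delivery, weeks | 38.9 (SD 2.5) | 40.2 | 99% |

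The ACOG outcome is "measured as receiving at least 20 out of 24 items from the ACOG standards of prenatal care list". The effective sample size can be as low as 135 per arm.

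Limitations and strengths states that the trial is underpowered for fetal or maternal death, low birth weight and receipt of standard care. Expected impact says of the study: "It will also provide evidence on whether this model is safe and effective".

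**The concern.** The utilization half of question 2 is a difference question, and a difference test suits it. The other half asks that nothing gets worse. A test of difference can reject equality, but failing to reject does not establish it, least of all when power is low. Under the stated rule the data can say that the arms differ. No result is defined that would say the care model left these outcomes unharmed.

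This matters because the declared aim is practice change. Fewer office visits are useful only if safety and care standards hold, so the no-worsening half carries as much weight as the utilization half. Without a criterion fixed in advance, the answer will be chosen after the results are known.

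**Working it through.** **Inputs.** From Sample size and Table 2: 135 per arm (150 enrolled per arm, up to 10% lost), two-sided alpha 0.05, and the rates, means and SD listed above. Assumed, because the article gives no acceptable worsening: 5 points for the two proportions, mirroring Table 2's own 5-point improvements, and 0.5 week for gestational age as an illustration.

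**Step 1: reproduce the plan's power.** For two proportions, power = Φ[(d − c − 1.96·SE0)/SE1], where SE0 = √(2·p̄(1−p̄)/n), SE1 = √((p1(1−p1)+p2(1−p2))/n), and c = 0 (uncorrected) or 1/n (continuity-corrected).

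- Low birth weight, 11% vs 6%, n = 135: SE0 = 0.0339, SE1 = 0.0338. Uncorrected 31%, corrected 23.9%. The corrected value matches the stated 24%.
- ACOG, 90% vs 95%: corrected 26.3% at n = 135 and 29.5% at n = 150. The latter matches the stated 30%.

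Both figures reproduce with the corrected test, though on different numbers per arm.

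**Step 2: power for a worsening of the same size, n = 135, uncorrected.**

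- Low birth weight, 11% to 16%: SE0 = 0.0416, SE1 = 0.0415. (0.05 − 1.96 × 0.0416)/0.0415 = −0.76, so power is 22%.
- ACOG, 90% to 85%: SE0 = 0.0403, SE1 = 0.0401. (0.05 − 1.96 × 0.0403)/0.0401 = −0.72, so power is 24%.

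At 150 per arm these become 24% and 26%. The corrected test that matches Table 2 gives less at n = 135: subtracting 1/135 = 0.0074 from the numerators yields z = −0.94 and −0.90, or 17% and 18%. The uncorrected figures are therefore the more favourable to the plan. For 80% power at 135 per arm the worsening would have to be about 12.9 points for low birth weight and 12.6 points for ACOG.

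**Step 3: gestational age.** SE = 2.5 × √(2/135) = 0.304 week.

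- A 1.3-week change in either direction: 1.3/0.304 = 4.27, power 98.9%. This matches the stated 99%.
- A 0.5-week change: 0.5/0.304 = 1.64, power 37%.

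**Step 4: what a null result leaves open.** 95% half-widths at 135 per arm with equal rates:

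- Low birth weight: 1.96 × √(2 × 0.11 × 0.89/135) = 7.5 points.
- ACOG: 1.96 × √(2 × 0.10 × 0.90/135) = 7.2 points.
- Gestational age: 1.96 × 0.304 = 0.6 week.

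Even with identical observed rates, a rise in low birth weight from 11% to about 18% (11 + 7.5 = 18.5) would remain compatible with the data.

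**Step 5: what a no-worsening criterion could deliver.** Chance that the 95% interval excludes a 5-point worsening when the arms are truly equal, Φ(0.05/SE − 1.96):

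- Low birth weight: SE = 0.0381, giving 26%.
- ACOG: SE = 0.0365, giving 28%.

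The smallest margin reaching 80% is (1.96 + 0.84) × SE, about 10.7 and 10.2 points.

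**The case against.** The strongest reply has four parts.

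- **The tests are two-sided and can detect harm.** This stands. It would be wrong to say that the 99% for gestational age protects only against a gain, because the same test has the same power for a 1.3-week loss. The weakness is that 1.3 weeks is a large difference, and that power for a 5-point worsening in the two proportions is only 22% to 24%.
- **The low power is disclosed.** It is, for low birth weight and standards of care, and the authors deserve credit. But disclosure does not say what result would answer question 2.
- **Nobody says non-significance will be reported as safe.** Correct. A reader might infer it, since P < 0.05 is the only rule given, but the article does not state it. Nor does Expected impact promise that the model will prove safe: it speaks of evidence on whether it is, which is an open question.
- **The plan need not rest on cut-offs.** Birth weight is abstracted, and t-tests are planned for continuous outcomes, so nothing rules out an analysis in grams. Only the ACOG threshold is explicitly a cut-off. Large power gains from continuous versions should not be claimed either. Under a normal-shift assumption the improvements in Table 2 would have 84% (ACOG) and 77% (birth weight) power, but the matching 5-point harms only 52% and 48%. That assumption is doubtful for a count capped at 24 items.

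Satisfaction is the named primary outcome and is untouched by this point.

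**Conclusion.** The mismatch is real. A question about not impacting outcomes is paired only with difference tests, its outcomes are sized for improvement, and no criterion is stated for a favourable answer. This is a rule the article states and that does not fit its own question, not a detail left to an unseen analysis plan.

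At 135 per arm, about 76% to 78% of trials would miss a 5-point worsening in ACOG fidelity or low birth weight. These figures rest on Table 2's usual-care rates and SD, on the lower sample size, and on the assumed 5-point and 0.5-week harms; at 150 per arm the picture barely changes. The confidence-interval half-widths need no assumed harm, only the usual-care rates, the SD and equal arms.

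The point limits what may be concluded under question 2. It does not show that the trial would be misreported, and it does not affect the primary outcome.

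**What to change.** For the maternal/fetal and ACOG outcomes under question 2:

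1. Report the between-arm difference with a 95% confidence interval. Conclude that there is no impact only if the interval excludes a largest acceptable worsening, fixed with reasons by the clinical team before analysis. Otherwise report the result as inconclusive. The alternative is to reword this half of question 2 as descriptive estimation, in line with the limitations section.
2. Add the expected half-widths to the Table 2 rows: about 7.5 points for low birth weight, 7.2 points for ACOG and 0.6 week for gestational age.
3. Optionally, report the ACOG item count and birth weight in grams as supplementary analyses, keeping the 20-of-24 threshold as specified.

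The cost is wording in the analysis plan and one table. Both supplementary measures come from records already being reviewed. Enrolment was under way and analysis is planned for the close of the study, so the rule can still be fixed in advance. The downside is that some safety conclusions will be inconclusive: with a 5-point margin that would be the usual result for the two binary outcomes even if the arms are truly equal.

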## Methods and design

### Study design

This study uses a hybrid effectiveness-implementation design in a single center randomized controlled trial (RCT) to compare the OB Nest intervention to usual care among low-risk pregnant women. Specifically, this is a Type 1 hybrid design as described by Curran and colleagues whereby the primary aim is a test of an intervention’s clinical effectiveness but there is also an a priori aim related to observing and gathering data on implementation [20]. Embedding process evaluation in an experimental design like an RCT allows researchers to answer both “Did it work?” and “How or why did it work (or not work)?” when studying complex interventions like those in health services [21]. This approach also has the potential to speed clinical uptake by delivering information on the intervention’s effectiveness in the study setting alongside data to inform external validity, such as the barriers and facilitators to widespread implementation [20, 22].

Mixed methods are well-suited for these types of implementation studies, where quantitative methods are used to test effectiveness and qualitative methods are used to understand process, participant perspectives (practitioners and consumers), and the intervention context [23, 24]. In this study, the quantitative methods are dominant *(QUAN),* supporting the primary aims of the study, and the qualitative methods are less dominant *(qual). QUAN* and *qual* data collection, as well as data analysis, will occur concurrently or simultaneously in a parallel mixed design [24].

